[figure not shown]

## LIST OF ABBREVIATIONS AND RELEVANT DEFINITIONS

| **ABR** | **ABR form, General Assessment and Registration form, is the application form that is required for submission to the accredited Ethics Committee (In Dutch, ABR = Algemene Beoordeling en Registratie)** |
| --- | --- |
| **ACOVE** | **Assessing Care Of Vulnerable elderly people** |
| **ADL** | **Activities of daily living** |
| **AE** | **Adverse Event** |
| **ALDS** | **AMC Linear Disability Score** |
| **AR** | **Adverse Reaction** |
| **CA** | **Competent Authority** |
| **CCMO** | **Central Committee on Research Involving Human Subjects; in Dutch: Centrale Commissie Mensgebonden Onderzoek** |
| **CGA** | **Comprehensive Geriatric Assessment** |
| **CN** | **Community Care Nurse** |
| **CRU** | **Clinical Research Unit** |
| **CV** | **Curriculum Vitae** |
| **DSMB** | **Data Safety Monitoring Board** |
| **EU** | **European Union** |
| **EudraCT** | **European drug regulatory affairs Clinical Trials** |
| **GCP** | **Good Clinical Practice** |
| **GP** | **General practitioner** |
| **HCN** | **Health Care Nurse (specialized in elderly care in general practice)** |
| **IADL** | **Instrumental Activities of Daily Living** |
| **IB** | **Investigator’s Brochure** |
| **IC** | **Informed Consent** |
| **ICOVE** | **Improving Care of Vulnerable elderly people** |
| **IMP** | **Investigational Medicinal Product** |
| **IMPD** | **Investigational Medicinal Product Dossier** |
| **ISAR-PC** | **Identification of Seniors at Risk in Primary Health Care** |
| **KOZ** | **Kring ouderenzorg** |
| **METC** | **Medical research ethics committee (MREC); in Dutch: medisch ethische toetsing commissie (METC)** |
| **NHP** | **Nursing Home Physician** |
| **NS** | **Clinical Nurse Specialist** |
| **OLVG** | **Onze Lieve Vrouwe Gasthuis** |
| **(S)AE** | **(Serious) Adverse Event** |
| **SPC** | **Summary of Product Characteristics (in Dutch: officiële productinfomatie IB1-tekst)** |
| **Sponsor** | **The sponsor is the party that commissions the organisation or performance of the research, for example a pharmaceutical**  **company, academic hospital, scientific organisation or investigator. A party that provides funding for a study but does not commission it is not regarded as the sponsor, but referred to as a subsidising party.** |
| **SUSAR** | **Suspected Unexpected Serious Adverse Reaction** |
| **Wbp** | **Personal Data Protection Act (in Dutch: Wet Bescherming Persoonsgevens)** |
| **WMO** | **Medical Research Involving Human Subjects Act (in Dutch: Wet Medisch-wetenschappelijk Onderzoek met Mensen** |

## SUMMARY

**Rationale:** Maintenance of functioning is an important feature of healthy aging. However, decline in functioning is common in community-dwelling older people. This can be related to an acute event, such as a hospital admission, or a more chronic condition, such as chronic disease, such as arthrosis. Most older people have capabilities to recover, but once certain (instrumental) activities of daily living (I)ADL appear to be lost, older people are at increased risk for further decline. New evidence shows that complex interventions can help elderly people to independently continue living at home, largely through prevention of the need for nursing-home care.

**Objective:** To prevent functional decline in community-dwelling elderly people of 70 years and older, through (1) screening for increased risk for functional decline; followed by

(2) a nurse-led comprehensive geriatric assessment (CGA) in patients at increased risk for functional decline, a tailor-made care and treatment plan, and seven follow-up contacts during one year.

**Study design:** A multicenter, cluster randomized clinical trial at the level of the General Practitioner (GP) comparing a pro-active, multi-component (multidisciplinary and multidimensional) intervention, coordinated by a Health Care Nurse (HCN) specialized in elderly care with care as usual.

**Study population:** Community-dwelling elderly people 70 years and older with an increased risk for functional decline.

**Intervention**: First, all eligible elderly people who are registered with their GP will be sent a postal questionnaire, the Identification of Seniors at Risk in Primary Care (ISAR-PC), that was developed during a pilot study. In half of the GP practices, patients with increased risk for functional decline will be invited to receive a nurse-led comprehensive geriatric assessment (CGA). In the CGA, participants will be screened for over 30 conditions on four domains (physical, functional, mental, social functioning) that are most prevalent among elderly people. The targeted problems are part of an evidence based protocol (‘toolkit’) that was developed in the Defence-study ([www.defencestudy.nl](http://www.defencestudy.nl/)) and further extended in a pilot phase of the FIT-study, and yields a care and treatment plan that is discussed with both patient and GP. When consensus is reached on the intervention, the HCN will coordinate all care and treatment contacts and will frequently see all participating elderly in the office or at home to monitor the effects of all interventions.

**Main study parameters/endpoints:** The main outcome is the the level of (instrumental) activities of daily living, measured with the modified Katz ADL index score. Secondary outcomes include hospital and nursing home admissions, self-reported health care utilization and quality of life (EQ-6D) and overall mortality.

**Nature and extent of the burden and risks associated with participation, benefit and group relatedness**

All elderly people with increased risk for functional loss will be subjected to a comprehensive geriatric assessment (appendix 2) that will approximately last one hour and is expected to take place in the GPs' surgery or at home (if the patient is not able to come to the GP practice). The identified problems are discussed with the GP and the patient and are translated into a care and treatment plan. Examples of potential interventions are consultations of an ergotherapist or physiotherapist for elderly people with increased fall-risk and/or impairments in their mobility. The nurses aim for 7 follow-up contacts within one year, through office consultations, home visits or telephone contact if warranted. The practice nurse will work in close collaboration with the GP, evaluating the care and treatment plans in the course of the follow-up, while looking out for emerging new problems over time.

Participants in the control group may not benefit from filling out the questionnaires, although their response will be analyzed over time and will be made available to their GP toward the end of the study, thus yielding potential new (or existing) problems that can be (further) addressed.

2. INTRODUCTION AND RATIONALE

In old age, reduction in physical function can lead to loss of independence, the need for hospital and long-term nursing-home care, and premature death. The importance of physical, functional, psychological, and social factors in realizing a healthy old age is recognized by elderly people, health-care professionals, and policy makers.

The risk factors for reduced physical function in elderly people, as identified in longitudinal studies, relate to comorbidities, physical and psychosocial health, environmental conditions, social circumstances, nutrition, and lifestyle. The need for a preventive strategy based around identification and treatment of diverse risk factors have been recognized in many western countries and many trials of complex interventions have been performed over the last decades. Complex interventions can be regarded as a combination of interdisciplinary teamwork for health and social problems. Trials have focused on general and frail elderly populations, elderly people discharged from hospital, and those at risk of falling. However, the development of risk factors, admission to hospital, and risk of falling represent a common chain of experiences for many elderly people. Likewise, multifactorial interventions in these populations have common characteristics and, in addition to targeting specific outcomes relating to hospital readmissions and falls, share the common aims of physical function maintenance, disability limitation, and promotion of independence.

Geriatric screening and multidimensional assessment are recognized in many European health care systems. In the US, managed care organisations focus mainly on frail elderly people and those discharged from hospital. Care is coordinated by case managers and this model has been applied in other countries, including England, where all individuals aged 75 and older receive a yearly assessment through nurse-led case management of elderly people.

Currently, many initiatives in the field of primary care for community-dwelling elderly people directed at prevention of functional loss and maintenance of independence are unfolding in the Netherlands, but whether or not health care nurses (HCN) should play a leading role in the coordination of care is still subject of debate. Nevertheless, it appears that comprehensive, integrated care for elderly people with (multiple) chronic conditions is lacking. Therefore, the regional geriatric network of the Academic Medical Centre in Amsterdam ('Kring Ouderenzorg AMC (KOZ)') has instigated the FIT-study (Functional decline In Transition). This study comprises a general screening to identify elderly people with increased risk for functional decline and a further diagnostic CGA to find problems that can be addressed through a care and treatment plan.

3. OBJECTIVES

#### Primary Objective

To prevent functional decline in community-dwelling elderly people of 70 years and older.

#### Secondary objectives

To prevent hospital admissions (1), nursing home admissions (2), disability (3), to improve quality of health and quality of life (4), and to describe met and unmet care needs (elderly and care-givers) (5).

4. STUDY POPULATION

**4.1. Population (base) and setting**

The study takes place in the Dutch primary health care setting in a region north of Amsterdam (region Alkmaar) and in some GP practices within the city of Amsterdam (North and South-East). All elderly subjects of 70 and older within the participating GP practices are invited to participate in the study. The structure of the Dutch healthcare system, in which virtually all inhabitants are registered with a GP, minimizes selection bias at this stage. The only exclusion criteria are prevalent dementia and disorders or circumstances expected to

interfere with successful participation in the geriatric assessments and follow-up.

Within the participating general practices a Health Care Nurse (HCN) who has specific and broad expertise in elderly care will play a central role in the assessments, development of a care and treatment plan and coordination of the provided care for the patient with all health care professionals involved.

**4.2 Inclusion criteria**

Phase 1 (general screening):

- Patients aged 70 years and older

Phase 2 (intervention)

- An increased risk for functional decline, defined as a score of two or more on the ISAR-PC screening instrument
- Speaks and understands Dutch
- Patient is registered with a GP

**4.3 Exclusion criteria**

- Terminal illness
- Dementia
- Does not speak or understand Dutch
- Living in a nursing home

**4.4 Sample size calculation**

The smallest difference with meaningful clinical relevance was determined at 0.5 points on the Katz-ADL15 (primary endpoint). Based on data from the pilot, this would represent a small effect size only (Cohen’s effect size of 0.20).

In this study, the intervention takes place at the level of the general practice, so this is also the unit of randomisation (cluster). Using a two-sided alpha of 0.01 and power of 90% (to keep the chances of spurious associations from multiple comparisons to a minimum) and assuming a design-effect of 1.08, in total 850 elderly people would need to receive both CGA and follow-up care. To allow for a drop-out rate of 40% (including patients who do not want treatment for identified problems, and patients who withdraw or die in the course of the study), in total around 1418 elderly people will have to receive CGA at the start of the intervention.

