**Total population ≥70 yrs**

**n=8220**

**Baseline measurement**

**n=5670**

**Increased risk: ±50%**

**Invitation for CGA**

**n=1418 (100%)**

**CGA**

**n=1134 (80%)**

**Intervention: 10/11 GP practices; N≈2835**

**Exclusion (6%, n=658):**

- Restricted life expectancy

- Dementia

- Planning to move

- Unable to speak Dutch

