In the control condition, the results of the postal questionnaires on patients with increased geriatric risk profiles will be made available to the GPs at the end of the intervention, to minimize contamination effects. Patients without increased risk in the in the intervention practices and all patients in the control practices will be blinded to the intervention through the use of a postponed informed consent procedure, described by Boter et al (2005). See also Figure 1 (5.1 ‘Study design’). This informed consent procedure is chosen to minimize Hawthorne effects among the patients who are not invited to attend the geriatric assessments and its successive follow-up. In the information letter to the patient, the purpose of the study will be explained, without specifically mentioning the intervention by the practice nurse. Targeted patients in the intervention group are further informed about the care coordination. After termination of the study, patients in both study groups will be informed about the research question and interventions that took place (*single-delayed consent design,* Schellings 2005).

The project will include the equivalent of 21 GP practices in the region of Alkmaar and will be randomised in a ratio of 1:1. Randomization is performed by the AMC Clinical Research Unit (CRU).

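### The sample size rests on an unsupported design effect of 1.08, which at this trial's cluster size means an intra-practice correlation of about 0.001; the 90% power depends on near-zero clustering

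*Protocol*

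**What the plan says.** Protocol section 4.4 sets the target on the primary endpoint: "The smallest difference with meaningful clinical relevance was determined at 0.5 points on the Katz-ADL15 (primary endpoint"), and adds from pilot data that "this would represent a small effect size only (Cohen’s effect size of 0.20"). The error rates follow: "Using a two-sided alpha of 0.01 and power of 90"%. Clustering enters through one number only, and the result is given in the same sentence: "assuming a design-effect of 1.08, in total 850 elderly people would need to receive both CGA and follow-up care". Section 4.4 allows 40% drop-out, which turns 850 into about 1418. The pilot is cited for the effect size, not for the design effect.

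The number of clusters comes from section 7.2: "The project will include the equivalent of 21 GP practices in the region of Alkmaar", allocated 1:1. The flow chart (Figure 1) has "Intervention: 10/11 GP practices; N≈2835" and the same for control. About half of these 2835 are at increased risk, which gives the 1418 invited. Figure 1 then shows 850 receiving care and seven follow-up contacts, in the intervention arm alone.

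Section 9 plans an intention-to-treat analysis with a linear multilevel model, patients nested within GPs, adjustment for baseline imbalance if necessary, and 99% confidence intervals.

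**The concern.** A design effect can be judged only through the ICC and the cluster size behind it. Section 4.4 gives neither, but the protocol's other figures put the cluster size at roughly 80 to 135 patients per practice (about 40 if 850 is both arms). At such sizes a design effect of 1.08 leaves almost no room for practices to differ. Yet the protocol expects some difference: the programme is delivered practice by practice through a nurse and GP, randomisation is stratified by practice size and social status score, and section 9 describes the Katz data as correlated within GPs.

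The 90% is the figure a reader will use to interpret a null result. If it holds only under near-zero clustering, section 4.4 should say so. The protocol also leaves unclear whether 850 is one arm or both, and the answer changes the power substantially.

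**Working it through.** **Inputs.** d = 0.20 (0.5 points, so an implied SD of 0.5/0.20 = 2.5), two-sided alpha 0.01, power 90%, design effect (DE) 1.08, 850 and 1418 patients (section 4.4); 21 practices at 1:1, taken as 10.5 per arm (section 7.2, Figure 1). The protocol gives no ICC, so every ICC other than those implied by 1.08 is an assumption, shown as a range.

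**Reproducing 850.** n per arm = 2(2.576 + 1.282)²/0.20² = 744. Times 1.08 = 804 per arm, or 1607 in both arms. Neither is 850. Of the variants tried (one- or two-sided, alpha 0.01 or 0.05, power 80% or 90%, per arm or both arms), only two-sided alpha 0.05 with 80% power for both arms together comes close: 393 × 2 × 1.08 = 849. The drop-out step does reproduce: 850/0.60 = 1417.

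**ICC implied by 1.08.** DE = 1 + (m − 1) × ICC, so ICC = 0.08/(m − 1).
- 850 per arm: m = 850/10.5 = 81, ICC = 0.08/80 = 0.0010 (0.00095 with 10 practices, 0.00105 with 11).
- 1418 per arm: m = 135, ICC = 0.08/134 = 0.0006.
- 850 in both arms (425 per arm): m = 40.5, ICC = 0.08/39.5 = 0.0020.

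**Power formula.** λ = 0.20 × √(n/(2 × DE)), with n per arm. Normal approximation: Φ(λ − 2.576). Small-sample version: non-central t on 21 − 2 = 19 df, critical value 2.861.

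**Power at the plan's own DE of 1.08.**
- 850 per arm: λ = 0.20 × √(850/2.16) = 3.967; 92% normal, 85% on 19 df. With DE = 1 (ICC zero), λ = 4.123 and power on 19 df is 88%.
- 1418 per arm: λ = 5.124; 99% normal, 98% on 19 df.
- 425 per arm: λ = 2.805; 59% normal, 49% on 19 df.

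**Largest ICC that keeps 90%.**
- Normal, 850 per arm: DE may reach 850/744 = 1.142, so ICC = 0.142/80 = 0.0018.
- Normal, 1418 per arm: DE may reach 1418/744 = 1.906, so ICC = 0.906/134 = 0.0068.
- On 19 df, 90% power needs λ = 4.236, that is 2 × 4.236²/0.20² = 897 per arm before any clustering. 850 is already below that. With 1418, DE may reach 1418/897 = 1.58, so ICC = 0.58/134 = 0.0043.

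**Power over assumed ICCs (normal / 19 df).**

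| Assumed ICC | 850 per arm: DE | Power | 1418 per arm: DE | Power |
|---|---|---|---|---|
| 0.005 | 1.40 | 81.8% / 72.6% | 1.67 | 93.9% / 88.0% |
| 0.01 | 1.80 | 69.1% / 59.1% | 2.34 | 81.7% / 72.5% |
| 0.02 | 2.60 | 49.3% / 40.5% | 3.68 | 57.9% / 48.3% |

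At ICC 0.02 the effective sample size per arm cannot exceed 10.5/0.02 = 525, short of the 744 needed, however many patients each practice contributes.

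**The case against.** A reader might infer that the trial simply fails to deliver its 90% power. The documents do not support that. They contain no ICC, so nothing in them shows that 0.001 is wrong. At the plan's own design effect, 850 per arm gives 92% on the normal approximation, and 804 would have been enough. The larger shortfalls in the table all come from assumed ICCs.

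A reader might also infer that the plan used a normal critical value where a small-sample one was needed. Section 4.4 states no formula, and the normal formula does not return 850. The degrees of freedom for the multilevel model may properly be left to a statistical analysis plan that is not at hand. What stands is that 850 per arm falls short of 90% on 19 df whatever the ICC.

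The strongest counter-argument concerns the denominator. The analysis is by intention to treat, section 5.2 sends the 12-month Katz questionnaire to everyone in both arms, and the 40% drop-out includes people who decline treatment but remain analysable. With up to 1418 per arm, power at 1.08 is 98% on 19 df. This is fair, with two limits. Deaths and withdrawals reduce 1418, and people who receive no care dilute the effect, so d = 0.20 may not carry over. Sections 4.4 and 7.5 themselves rest the power on 850.

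Other uncertainties run both ways. Stratification and baseline adjustment may reduce residual clustering; unequal practice sizes would raise the design effect. Section 7.2 counts the equivalent of 21 practices, while sections 5.1 and 9 refer to the GP level; more and smaller clusters would raise the ICC implied by 1.08. The 99% confidence intervals would show the imprecision of a null result, but they do not correct the stated power.

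**Conclusion.** The point holds as one of an unsupported and highly sensitive assumption. A design effect of 1.08 means an ICC of 0.0006 to 0.002, depending on which of the protocol's patient counts is meant, and section 4.4 gives no basis for it. With 850 per arm, 90% power requires an ICC below about 0.0018 on the normal approximation and is not reached at any ICC on 19 df. With 1418 per arm and an undiluted effect, the tolerable ICC rises to about 0.007 or 0.004. If the words in total are meant literally, power is 59% or 49% even at 1.08.

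These results assume d = 0.20, 10.5 equal-sized practices per arm and no gain from baseline adjustment. That the true ICC exceeds these limits is not shown.

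**What to change.** In section 4.4:
- State whether 850 is per arm or both arms together, reconcile this with Figure 1, and show the calculation that yields it at the stated alpha and power.
- Replace the bare 1.08 with the ICC, its source, the mean cluster size and DE = 1 + (m − 1) × ICC.
- Restate power for 21 practices with a small-sample df, over a range of ICCs, for the population to be analysed under intention to treat, saying what effect is assumed in people who receive no care plan.

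As a guide only, an ICC of baseline Katz can be estimated without comparing arms, because the baseline questionnaire goes to both. Restrict it to patients with ISAR-PC of 2 or more, and note that it may differ from the ICC of the 12-month outcome adjusted for baseline. An ICC from all 5670 respondents would describe a different population from the primary comparison.

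The cost is a rewritten paragraph, one pooled calculation and a less favourable stated power. No extra patients are needed.

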9. STATISTICAL ANALYSIS

Statistical analyses will be based on an intention-to-treat principle. Baseline assessments and outcome parameters will be summarized using simple descriptive statistics. The main analysis focuses on a comparison of patients with a similar risk profile (based on ISAR-PC and Katz-ADL scores in both groups). As the Katz-ADL data will have a correlated multilevel structure (patients are ‘nested’ within their GPs) difference between these scores will be analyzed using a linear mixed, multilevel model. If necessary, we will adjust the effect size for baseline imbalance. The same (linear and logistic) multi-level approach will be used with regard to the secondary outcome parameters, including survival rates. Survival data will be additionally analyzed using Kaplan-Meier survival curves and the log-rank test.

We will perform a predefined subgroup analysis for patients with baseline ‘high’ and ‘low’ risk scores (ISAR-PC≥2,5 and less, based on pilot-assessments) on all primary and secondary outcomes. In all analyses statistical uncertainties will be quantified via corresponding 99% confidence intervals.

Finally, process outcome data will be analyzed qualitatively within the theoretical framework of the adaptive implementation model (Meiland 2005).

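### Section 4.4 handles non-uptake as drop-out by dividing by 0.6, but the intention-to-treat analysis keeps those patients in, so the stated 90% power does not follow

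*Protocol*

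**What the plan says.** Section 4.4 sets the target at 0.5 points on the 15-item Katz, expressed as a standardised "effect size of 0.20". The other inputs are given as "Using a two-sided alpha of 0.01 and power of 90" per cent and "assuming a design-effect of 1.08". The section concludes that "in total 850 elderly people would need to receive both CGA and follow-up care". It then raises the number to about 1418: "To allow for a drop-out rate of 40% (including patients who do not want treatment for identified problems, and patients who withdraw"; deaths are listed in the same bracket. Section 7.5 repeats the step from 850 to 1418.

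Figure 1 shows where the 40% goes in the intervention arm. Of 1418 invited to CGA, 284 (20%) do not respond. Of the 1134 assessed, 284 (25%) have no care or treatment plan. That leaves 850 (60%) who receive care and follow-up contacts.

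Section 9 states: "Statistical analyses will be based on an intention-to-treat principle". It adds: "The main analysis focuses on a comparison of patients with a similar risk profile (based on ISAR-PC and Katz-ADL scores in both groups"). Section 5.2 sends the 12-month Katz questionnaire to everyone in both arms, and section 7.6 provides telephone follow-up of those who withdraw.

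**The concern.** Dividing by 1 minus the drop-out rate is right when the people concerned supply no outcome and so leave the analysis. Someone who declines CGA or has no care plan is a different case. The protocol plans to collect that person's 12-month Katz and, under ITT, to analyse it in the intervention arm. Such patients leave n unchanged and pull the arm's mean towards that of the controls. If a fraction p of the full effect survives, the sample size must grow by 1/p², not 1/p.

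The 90% power is the basis for reading a null result on the primary endpoint. If it was worked out for receivers but the analysis covers everyone at risk, it does not describe the planned comparison. Figure 1 also uses the entire 40% for non-uptake, so nothing in it is left for patients whose 12-month Katz is truly missing.

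**Working it through.** **Inputs.** From section 4.4: difference 0.5 points, d = 0.20 (implied SD 0.5/0.20 = 2.5), two-sided alpha 0.01, power 90%, design effect 1.08. From Figure 1: 60% of at-risk patients receive care, and about 50% of roughly 2,835 respondents per arm are at risk, which is about 1,418 per arm. Normal quantiles: 2.5758 + 1.2816 = 3.8574.

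**The plan's own figures.**
- n per arm = 2 × 3.8574² / 0.20² × 1.08 = 744 × 1.08, about 804. The stated 850 is not reproduced exactly. Read as one arm, as Figure 1 shows it, 850 is slightly generous and gives 91.8% power.
- 850 / (1 − 0.40) = 1,417, against about 1418. This step reproduces.
- Figure 1: 0.80 × 0.75 = 0.60. The two non-uptake steps account for the whole 40%.

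**Non-receivers kept in, with 0.5 as the effect in receivers and zero effect in the rest.**
- ITT difference = 0.60 × 0.5 = 0.30 points; d = 0.60 × 0.20 = 0.12.
- n per arm = 2 × 3.8574² / 0.12² × 1.08, about 2,232. The factor is 1/0.36 = 2.78, where the plan used 1/0.60 = 1.67.
- Power at 1,418 per arm: 0.12 × √(1418 / (2 × 1.08)) = 3.07; 3.07 − 2.58 = 0.50; power about 69%.

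**Range by share of the 0.5 points retained in the ITT contrast** (1,418 per arm, no outcome loss, design effect held at 1.08):

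| Share retained | ITT difference (points) | d | Power |
| --- | --- | --- | --- |
| 60% | 0.30 | 0.12 | 69% |
| 70% | 0.35 | 0.14 | 84% |
| 75% | 0.375 | 0.15 | 90% |
| 80% | 0.40 | 0.16 | 94% |
| 100% | 0.50 | 0.20 | 99.5% |

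The 75% row requires non-receivers to gain about (0.75 − 0.60)/0.40 = 0.375 of the full effect. The 100% row is the case where 0.5 is already the whole-group difference. If non-receivers gained nothing, that would need 0.5/0.6 = 0.83 points in receivers.

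**Outcome loss.** The protocol gives no rate for a missing 12-month Katz, so 10% and 20% are assumptions. Starting from 69%, loss unrelated to uptake gives 63% and 57%. Loss confined to non-receivers gives 75% and 81%, because the diluting patients are then the ones who leave.

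**The case against.** The strongest reply is that section 4.4 introduces 0.5 as the smallest clinically relevant difference and never confines it to receivers. If it is the whole-group difference, 1,418 per arm is more than ample and the inflation errs on the safe side. That reading is open and cannot be ruled out. It does not rescue the calculation, because refusers would then need no inflation at all, and the section frames its 850 as people who receive the intervention.

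A second reply is that the 40% is not all untreated. Half of the non-receivers in Figure 1 (284 of 568) did have the CGA, and section 4.4 also counts withdrawals and deaths. This stands in part. It makes zero effect in all non-receivers a worst case, and it is why a range is needed. Figure 1 nevertheless gives the whole 40% to non-uptake, so the text and the figure do not agree on what the 40% contains.

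Some stronger inferences are tempting but not supported:
- A reader might infer that the risk-profile sentence in section 9 breaks ITT or creates a further, undefined population. It rests on baseline scores collected in both arms before CGA, and section 4.2 gives ISAR-PC of two or more. Selecting both arms on the same baseline score is compatible with ITT. Only the role of the Katz score is left loose.
- A reader might infer that the treated 850 will be compared with controls. That would be selection-biased, since controls are never offered CGA, but no section proposes it.
- A reader might take the 25% non-response in Figure 1 as the 12-month loss rate. It is non-response to the first mailing among all eligible people, not later loss among those who had responded.

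**Conclusion.** The point holds. Section 4.4 corrects for non-uptake as though those patients left the analysis, while sections 5.2, 7.6 and 9 keep them in. The stated 90% therefore does not follow from the planned analysis. Before any outcome loss, power runs from about 69% to about 99.5%, according to what 0.5 points refers to and what non-receivers gain; 90% arises only if about 75% of the effect is retained.

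The documents do not support saying flatly that the trial is underpowered. The 69% and the 2,232 per arm rest on two assumptions: that 0.5 applies to receivers only, and that non-receivers gain nothing. If both are true, the roughly 1,418 at-risk patients per arm in the planned practices cannot supply the number needed. All figures take the design effect of 1.08 as given and read 850 as the intervention arm, as in Figure 1.

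**What to change.** In section 4.4, and where section 7.5 repeats it:
- State whether 0.5 points is the ITT difference or the difference in patients who receive care.
- Restate power for the ITT set, with CGA and care uptake (60%) acting on the effect size and loss of the 12-month Katz acting on n, as two separate inputs. Since the protocol gives no loss rate, state it as an assumption and show a range.
- Make the contents of the 40% agree with Figure 1.

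In section 9, state that the main comparison is all respondents with ISAR-PC of two or more in both arms, regardless of CGA uptake, with baseline ISAR-PC and Katz as covariates. An estimate of the effect in accepters may be added as a secondary analysis but is not required.

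The cost is protocol wording and one recalculation. The stated power may fall, and if the receivers-only reading is the intended one, the planned practices may not suffice for 90%.

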**7.5 Replacement of individual subjects after withdrawal**

A total of 850 patients are needed to receive CGA, individual care plan and follow-up during one year to obtain sufficient power. After correction for 40% drop-out (see Figure p.14), around 1418 participants are needed to enrol in the CGA.

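### Sections 4.4 and 7.5 require about 1418 people to receive CGA, but Figure 1 has 1418 invited and 1134 receiving it, and its two losses use up the whole 40% drop-out allowance

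*Protocol*

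**What the plan says.** Section 4.4 sets the target: "in total 850 elderly people would need to receive both CGA and follow-up care". It then inflates that target: "To allow for a drop-out rate of 40% (including patients who do not want treatment for identified problems, and patients who withdraw or die" during the study). The result is that "in total around 1418 elderly people will have to receive CGA at the start of the intervention".

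Section 7.5 gives the same count, that "around 1418 participants are needed to enrol in the CGA", and names its source: "After correction for 40% drop-out (see Figure p.14"). It also says that the 850 must have CGA, a care plan and a year of follow-up for the study to have enough power. The figure on that page is taken to be Figure 1: the contents list puts section 5 on page 13, and the chart is announced there for the next page.

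Figure 1 starts from about 2835 respondents in the intervention practices and a share of "Increased risk: ±50"%. It then shows:
- invitation for CGA: 1418 (100%)
- no response to the invitation: 284 of 1418 (20%)
- CGA: 1134 (80%)
- no care or treatment plan: 284 of 1134 (25%)
- care with seven follow-up contacts: 850 (60%)

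The chart has no later loss step.

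**The concern.** The same number, 1418, counts people assessed in the text and people invited in the chart that the text cites. The same 40% covers different losses in the two places. In section 4.4 it is a loss from people who have had CGA, and it includes withdrawal and death. In Figure 1 it is made up of people who never reach CGA and people who have CGA but no plan.

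Two things are at stake. First, nobody can tell from the protocol whether 1134 completed assessments would meet the plan or fall 20% short of it (284/1418 = 20%). Second, the population is aged 70 and over and at increased risk, and the primary outcome is a Katz score at 12 months. Some people will die or not return the form. Section 4.4 says that deaths and withdrawals are covered, but the chart has nothing left to cover them.

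**Working it through.** **Inputs.** From section 4.4: target 850, drop-out 40%, "Using a two-sided alpha of 0.01 and power of 90"%, "Cohen’s effect size of 0.20" and a design effect of 1.08. From Figure 1: 2835, 50%, 1418, 1134, 850 and the two counts of 284. From section 7.2: allocation 1:1.

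**The plan's own figure.** 850 / (1 − 0.40) = 1416.7, about 1417, which agrees with 1418. Figure 1 reaches 1418 by another route: 2835 × 0.50 = 1417.5. The number is right as arithmetic; the conflict is over whom it counts.

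**The chain in Figure 1.**
- 1418 × 0.80 = 1134
- 1134 × 0.75 = 850.5
- 0.80 × 0.75 = 0.60
- 284 + 284 = 568, and 568 / 1418 = 40.06%

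The two boxes account for the whole 40%.

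**Text against chart.**
- People receiving CGA: 1418 in the text and 1134 in the chart, a difference of 284.
- Loss after CGA that still leaves 850: 40% in the text, and 1 − 850/1134 = 25% in the chart. The no-plan box takes all of that 25%.
- The 284 non-respondents are lost before CGA, so they cannot be part of a drop-out counted from people who received it.

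**Is 850 per arm or total?** The usual formula gives n per arm = 2 × (2.576 + 1.282)² / 0.20² = 744. Multiplied by 1.08, this is about 804 per arm, or 1607 in total. So 850 is somewhat above the per-arm requirement and about half the total one. Section 4.4 says 'in total', but Figure 1 places 850 in the intervention arm alone.

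**Power, as illustration only.** Power = Φ(d × √(n / (2 × 1.08)) − 2.576), with n per arm.
- n = 850, d = 0.20: 0.20 × √(850/2.16) = 3.97, power about 92%.
- n = 765 (an assumed 10% further loss), d = 0.20: 3.76, power about 88%.
- n = 425 (850 read as the total), d = 0.20: 2.81, power about 59%.

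**Power if all at-risk patients are analysed.** Assume 1418 per arm, that is, the same 50% at-risk share in the control practices.
- No missing outcomes: about 99% at d = 0.20. If 0.20 is the effect in those who get care, and the 40% without care gain nothing, then d = 0.20 × 0.60 = 0.12 and power is about 69%.
- 10% missing (1276 per arm): about 99% and 63%.

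The answer depends mainly on whether 0.20 already allows for uptake, which the protocol does not say.

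**The case against.** The strongest reply is that the labels are wrong but the design may not be. Section 9 analyses by intention to treat and compares patients of similar risk in both groups. Section 5.2 sends the 12-month questionnaire to everyone in both arms. People who decline CGA or have no plan can therefore still supply a Katz score. On that basis the intervention arm starts from about 1418 at-risk patients, and even 40% missing outcomes would leave about 850. Section 7.6 also provides telephone follow-up for people who withdraw, so withdrawal need not mean a lost outcome.

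This reply stands as far as power is concerned. A reader might infer that the trial cannot deliver the 850 people with one year of follow-up. The documents do not show that, for the reasons just given. The box with 850 people and seven contacts could also be meant as those who complete the contacts.

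A reader might also apply the 40% to the 1134 assessed and conclude that only about 680 remain. That counts part of the allowance twice, because 1134 is already net of the 20% non-response that makes up half of the 40%. Nor can it be said that about 1773 people (1418/0.80) must be invited. That holds only if the wording of section 4.4 is the real requirement, whereas the text may simply have called invitees recipients.

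The reply does not remove the contradiction. On any reading, sections 4.4 and 7.5 disagree with the chart that 7.5 cites. The deaths and withdrawals that 4.4 says are included appear nowhere in that chart. Non-uptake that does not remove patients is also not drop-out; it dilutes the effect and belongs in the effect size.

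**Conclusion.** The inconsistency is certain and rests on the protocol's own figures: 284 fewer people receive CGA in Figure 1 than the text requires, and 568/1418 = 40.06% exhausts the allowance. No loss for death, withdrawal or a missing 12-month Katz is shown.

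The size and even the direction of the change in power are not settled. If 850 is per arm and is the number analysed, an assumed 10% further loss takes power from about 92% to about 88%, just below the 90% target. Under intention to treat with all at-risk patients, it could be well above or well below 90%, depending on how non-uptake enters the effect size. This should be corrected as a misstated sample-size basis; it is not evidence that the trial is underpowered.

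**What to change.** 1. In sections 4.4 and 7.5, replace the statement that 1418 receive or enrol in CGA with: 1418 invited, about 1134 receiving CGA, about 850 with a care plan. If another meaning is intended, reconcile the text and Figure 1 on that meaning.
2. Split the 40% into two parts. One is non-uptake (no response, or no plan), which under intention to treat dilutes the effect but does not remove patients. The other is a separate rate of loss of the 12-month Katz through death, withdrawal or non-return.
3. State whether 850 is per arm or total.
4. Restate the expected number per arm with a 12-month Katz and the power for that number, using an effect size that allows for the planned uptake.

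The cost is a text correction in two sections and one recalculation. The relabelling itself needs no extra patients. Whether the recalculated power is better or worse than stated cannot be said in advance.
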